##### Outcomes

The outcomes of the study will include the following:

1. Prevalence of colorectal cancer and advanced colorectal neoplasia in patients with CKD

2. Screen positivity rate: defined as the proportion of participants with positive screens in the total screened study population

3. Test sensitivity: defined as the number of colorectal cancers and/or advanced neoplasms detected through screening divided by the total number of colorectal cancers and/or advanced neoplasms detected through screening and the total number of cancers and/or advanced neoplasms occurring within the delay in a given period (the follow-up time) after a negative screen.

4. Test specificity: defined as the number of participants with no colorectal cancers and/or advanced neoplasms within the follow-up period divided by the number of participants with no colorectal cancers and/or advanced neoplasms after a negative screen and the number of participants without colorectal cancers and/or advanced neoplasms after a positive screen within the follow-up period.

5. Participation rate of screening among individuals with CKD.

6. Potential harms of screening and the diagnostic colonoscopies, such as bleeding, bowel perforation and the inherent risks of peritonitis, particularly among peritoneal dialysis patients.

7. Direct healthcare costs, including individually- collected screening, diagnostic, treatment and overhead costs.

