##### Statistical analyses and sample size calculations

Sensitvity and specificity of iFOBT screening for advanced colorectal neoplasia and cancer will be estimated for (i) CKD (stages 3-5) patients, (ii) dialysis patients, and (iii) transplant patients. For each estimate, the required sample size will be determined by the combined expected prevalence of advanced neoplasia and cancer, the expected sensitivity and specificity, and the required precision of the estimated maximum 90% confidence interval width. For each of the three patient groups, the sensitivity is expected to be 75% and the maximum required 90% confidence interval width is ± 10%. Therefore, 51 cases of advanced neoplasms and cancer will be required. The total sample size and the precision of the estimates of specificity (which is expected to be 90%) for each patient group will be determined by the expected prevalence for that group. In the CKD stages (3-5) group (with a one-year combined estimated prevalence of disease equals to 3.1%), a total of 1637 patients would yield 51 cases and 1586 non-cases. The maximum 90% confidence interval width for specificity is ± 1.3%. Among those on dialysis (with a one-year combined prevalence of disease equals to 3.94%), a total of 1288 patients would yield 51 cases and 1237 non-cases, giving a maximum 90% confidence interval width for specificity of ± 1.4%. Assuming a one-year combined prevalence of disease equals to 4.2% in the transplant population, a total of 1208 patients will again yield a total of 51 cases and 1157 non-cases, giving a maximum 90% confidence interval width for specificity of ± 1.5%.

Across all 3 groups, a total of 4133 participants are required over a 5-year screening period. Assuming a participation rate of 68%, a population size of 6077 CKD patients is required to achieve the target sample size of 4133 for any meaningful analyses.

These sample sizes will provide 80% power to detect a difference of between 3% and 4% in specificity between groups of patients. The small number of expected cases does not allow comparisons in sensitivity to be made between groups.

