#### Study design 2: Cost-effectiveness and cost-utility analyses

Using individually-collected clinical estimates such as the prevalence of disease, the test sensitivity and specificity of iFOBT, the screening participation rate, the probability of cancer and adenoma diagnoses, direct costs estimates and utility weights from the diagnostic test accuracy study and from published clinical estimates of randomised controlled trials of screening, trial and modelled -based cost-effectiveness and cost-utility analyses will be conducted to estimates the efficiency of colorectal cancer screening in CKD.

Probabilistic decision analytical models will be developed to estimate the incremental costs and health benefits of screening compared with no screening in the CKD population. Using time-dependent transition probabilities, the models will provide the analytical framework to simulate the natural history of colorectal neoplasms, the screening and the diagnostic process and the outcomes of colorectal neoplasms in individuals with CKD.

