## Discussion

The DETECT study is a detailed analysis of the diagnostic test performance characteristics of iFOBT screening, the costs and health benefits of screening in the CKD population and of patient perspectives and preferences regarding colorectal cancer screening. Specifically, this proposed program of research will provide:

1. Estimates of the prevalence for pre-malignant and malignant colorectal neoplasms in the CKD population

2. Estimates of test performance characteristics such as test sensitivity and specificity of iFOBT screening in individuals with CKD

3. Estimates of screening participation rate in people with CKD

4. The incremental costs and health outcomes of iFOBT screening in CKD

5. Patients' perspectives, attitudes, beliefs experiences and preferences regarding screening colorectal cancer

Findings of our research will address the critical issues in chronic disease prevention in Australia and worldwide. This project is uniquely placed to investigate the evidence gaps surrounding the diagnostic test accuracy, the costs and benefits and patients' perspectives and preferences for colorectal cancer screening, with the ultimate objective being to improve the survival and quality of life outcomes in patients with CKD.

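### For advanced neoplasia, the prevalence outcome is close to an iFOBT detection rate: up to a quarter of disease goes unascertained at full colonoscopy uptake, and the economic model inherits the gap

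*Protocol article*

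**What the plan says.** The Outcomes list of Study design 1 opens with "Prevalence of colorectal cancer and advanced colorectal neoplasia in patients with CKD", without a numerator, a denominator or a correction. The Discussion promises it again: "Estimates of the prevalence for pre-malignant and malignant colorectal neoplasms in the CKD population".

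Three other sections determine what can be observed:

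- **Diagnostic procedures:** colonoscopy is offered, by invitation, to participants with a positive iFOBT. Advanced neoplasia is defined by size, villous component or high-grade dysplasia.
- **Reference standard:** all participants have clinical follow-up for two years. Linkage to the state cancer registry at 2, 5 and 7 years is described as capturing cancer diagnoses.
- **Outcomes, items 3 and 4:** disease in a screen-negative participant counts only if it appears during follow-up.

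The sample size section assumes "the sensitivity is expected to be 75% and the maximum required 90% confidence interval width is ± 10" percentage points and concludes: "Therefore, 51 cases of advanced neoplasms and cancer will be required". Study design 2 then builds the economic analysis as follows: "Using individually-collected clinical estimates such as the prevalence of disease, the test sensitivity and specificity of iFOBT", together with other study data and published trial estimates.

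**The concern.** Prevalence needs disease status in everyone, or in a sample with known selection. Advanced adenoma can be established only by endoscopy and histology, and here endoscopy is planned only after a positive test. A lesion in a screen-negative participant is seen only if it happens to surface clinically. For advanced neoplasia the reported figure will therefore depend on how sensitive the test is, which is the quantity the study sets out to measure.

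Unseen screen-negative disease drops out of two estimates at once. It lowers prevalence, and it removes false negatives from the sensitivity denominator. Study design 2 takes both estimates as inputs. At stake are the first listed outcome and two model quantities: disease missed under screening, and baseline neoplasia in the no-screening arm. Probabilistic analysis around the observed values reflects sampling error, not this bias.

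**Working it through.** **Inputs from the sample size section.** Sensitivity 75% with a 90% interval of ±10 points; specificity 90%; 51 cases per group; prevalences 3.1%, 3.94% and 4.2%; group sizes 1637, 1288 and 1208.

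**Reproducing the plan.** Cases needed = 1.645² × 0.75 × 0.25 / 0.10² = 50.73, rounded up to 51. Group size = 50.73 / prevalence gives the stated sizes almost exactly (size × prevalence is 50.74 to 50.75 in each group). They sum to 4133. The plan's arithmetic stands.

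**Who is examined.** In CKD stages 3-5, expected screen-positives are 0.75 × 51 + 0.10 × 1586 = 197 of 1637, or 12%. The other 88% have no planned colonoscopy.

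**Disease found at the screen, full uptake.** 0.75 × 51 = 38.25 cases found; 51 − 38.25 = 12.75 (25%) not found.

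| Group | Found at screen | Assumed prevalence | Found at screen if uptake is 80% (assumption) |
|---|---|---|---|
| CKD 3-5 | 38.25/1637 = 2.34% | 3.1% | 30.6/1637 = 1.87% |
| Dialysis | 38.25/1288 = 2.97% | 3.94% | 30.6/1288 = 2.38% |
| Transplant | 38.25/1208 = 3.17% | 4.2% | 30.6/1208 = 2.53% |

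**Adding follow-up.** Let u be colonoscopy uptake after a positive screen and f the share of screen-negative disease that surfaces in follow-up. The article gives neither, so both are assumptions shown over a range.

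- Shortfall in prevalence = 1 − (0.75u + 0.25f)
- Apparent sensitivity = 0.75u / (0.75u + 0.25f)

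At u = 100%:

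| f | Cases identified of 51 | Shortfall | Apparent sensitivity |
|---|---|---|---|
| 0% | 38.25 | 25.0% | 100% |
| 25% | 41.4 | 18.8% | 92.3% |
| 50% | 44.6 | 12.5% | 85.7% |
| 100% | 51 | 0% | 75% |

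At full uptake the shortfall is 0.25(1 − f), so 25% is its ceiling. If f = 50%, a shortfall of 25% or more requires 0.75u + 0.125 ≤ 0.75, that is u ≤ 83%. Sensitivity is overstated whenever f is below u.

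**What reaches the model.** Apparent prevalence × apparent sensitivity = 38.25/N at full uptake, whatever f is. This equals the true screen yield, so the yield is preserved. What changes is the number of false negatives (12.75f instead of 12.75) and total neoplasia (38.25 + 12.75f instead of 51).

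**The case against.** A reader might infer that the plan misses at least a quarter of disease on its own figures. The documents do not support that. Outcome 1 does not confine the numerator to screen-detected disease, all participants are followed for two years, and the sensitivity definition counts disease appearing after a negative screen. At full uptake a quarter is the maximum, and going beyond it needs an uptake figure the article does not give.

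A reader might also infer that the whole outcome depends on the test. For cancer it does not: notification is statutory and linkage covers everyone. The risk for cancer may run the other way, since linkage at 5 and 7 years can add cancers that arose after the screen. That would raise apparent prevalence and lower apparent sensitivity.

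Nor can one infer that the cost-effectiveness ratio is biased in a known direction. The screen yield is preserved, the model also draws on published trial estimates, and the article does not show how the two sources are combined. That detail may properly sit in a fuller document.

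These points limit the size and scope of the concern. They do not remove it: who is verified is fixed by the Diagnostic procedures and Reference standard sections, and a later analysis plan cannot recover lesions that nobody looked for.

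**Conclusion.** The point holds for advanced neoplasia and for the composite of cancer and advanced neoplasia. What the study can deliver there is close to a detection rate among participants screened, with an unknown addition from follow-up. Taking 75% sensitivity as the plan does, the understatement of prevalence lies between 0 and 25% at full colonoscopy uptake and can be larger only with incomplete uptake. Observed sensitivity is too high whenever a smaller share of screen-negative than of screen-positive disease is ascertained. That is the likely situation for adenomas, given the absence of any planned search in screen-negatives. In the economic model, disease missed under screening and baseline neoplasia without screening would be understated if these observed values were used unadjusted. The effect on the cost-effectiveness ratio cannot be calculated from the article. The position for cancer alone is separate and depends on the linkage window.

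**What to change.** **Outcomes item 1 and Discussion item 1.** Report advanced neoplasia and the composite as a detection rate per participant screened, and show cases surfacing in follow-up separately. Report cancer on its own over one fixed window.

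**If prevalence is quoted.** Derive it as screen-detected rate / (observed colonoscopy uptake × sensitivity) over a stated sensitivity range, and label it model-dependent. Leave follow-up cases out of the numerator, otherwise the formula overcorrects. For CKD stages 3-5 at full uptake, with an illustrative range of 50% to 90%, this gives 2.34/0.50 = 4.7% down to 2.34/0.90 = 2.6%.

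**Study design 2.** Do not use the observed adenoma prevalence and sensitivity as the sole inputs. Add a scenario analysis over the corrected range, including published colonoscopy-verified values. These should not simply replace the study's estimates: the Background argues, as its first reason for the study, that general-population test characteristics do not generalise to CKD.

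**Cost.** Changed wording, one derived table and one added model scenario, with no new procedures. The price is a wider range for prevalence and for the model results.

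### Sensitivity is worded as a ratio of lesion counts, while specificity, screen positivity and the sample size count people; taken literally, sensitivity could be biased upward

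*Protocol article*

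**What the plan says.** The Outcomes list of Study design 1 uses two units of count.

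- **Sensitivity (item 3)** is "defined as the number of colorectal cancers and/or advanced neoplasms detected through screening divided by the total number of colorectal cancers and/or advanced neoplasms" in two parts: those found by screening, and "the total number of cancers and/or advanced neoplasms occurring within the delay in a given period (the follow-up time) after a negative screen". Numerator and denominator both count lesions.
- **Screen positivity (item 2)** is "defined as the proportion of participants with positive screens in the total screened study population".
- **Specificity (item 4)** is "defined as the number of participants with no colorectal cancers and/or advanced neoplasms within the follow-up period", divided by the unaffected screen-negatives plus "the number of participants without colorectal cancers and/or advanced neoplasms after a positive screen". It counts people throughout.

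The section on statistical analyses and sample size states that "the sensitivity is expected to be 75% and the maximum required 90% confidence interval width is ± 10" percentage points, and concludes: "Therefore, 51 cases of advanced neoplasms and cancer will be required". It then treats those cases as people. In the CKD stages 3-5 group, "a total of 1637 patients would yield 51 cases and 1586 non-cases". The dialysis and transplant groups are built the same way (51 + 1237 = 1288 and 51 + 1157 = 1208).

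Three other statements bear on the point. Under Screening procedure, a kit is positive if either of its two stool samples reaches the threshold, so each person has one result. Under Diagnostic procedures, participants with a positive screen are invited to colonoscopy. Under Reference standard, everyone is followed clinically for two years, with later linkage to the state cancer registry. No section says how a person with more than one lesion is counted.

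**The concern.** The test is read once per person, so the natural unit for sensitivity and specificity is the person. All lesions in one person share one iFOBT result. If sensitivity counts lesions while specificity counts people, the two cannot be read from the same 2x2 table, and sensitivity is not the quantity for which the study was sized.

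The direction of a possible error can also be foreseen. A colonoscopy after a positive screen can record several advanced adenomas at once. A screen-negative participant has no planned colonoscopy, and clinical follow-up with cancer registration is less likely to record several lesions in one person. If so, multiple lesions would weigh more on the detected side of the ratio than on the missed side.

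Sensitivity is central to the first aim, and Study design 2 lists it among the inputs to the cost-effectiveness analyses, so an upward shift would carry into them.

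**Working it through.** **Step 1. Reproduce the 51 cases and identify their unit.** Inputs from the sample size section: p = 0.75, half-width d = 0.10, 90% confidence (z = 1.645).

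n = z² p(1 − p)/d² = 1.645² × 0.75 × 0.25/0.10² = 50.73, rounded up to 51.

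Dividing 50.73 by each group's prevalence gives:

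| Group | Prevalence | 50.73/prevalence | Stated total |
|---|---|---|---|
| CKD stages 3-5 | 3.1% | 1636.4 | 1637 |
| Dialysis | 3.94% | 1287.5 | 1288 |
| Transplant | 4.2% | 1207.8 | 1208 |

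Rounded up, all three match. Cases plus non-cases equal patients in each group, so the 51 are independent people. Their half-width is 1.645 × √(0.1875/51) = ±9.97 points. The stated figures are right for a person-level sensitivity.

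**Step 2. Apply item 3 literally.** Let m1 and m0 be the mean numbers of recorded lesions per affected screen-positive and per affected screen-negative person. The protocol gives neither, so both are assumptions. With a person-level sensitivity of 75%:

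lesion-level sensitivity = 0.75 m1/(0.75 m1 + 0.25 m0)

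| m1 | m0 | Calculation | Sensitivity | Shift (points) |
|---|---|---|---|---|
| 1.1 | 1 | 0.825/1.075 | 76.7% | 1.7 |
| 1.25 | 1 | 0.9375/1.1875 | 78.9% | 3.9 |
| 1.5 | 1 | 1.125/1.375 | 81.8% | 6.8 |
| 2.0 | 1 | 1.5/1.75 | 85.7% | 10.7 |
| any | equal to m1 | m1 cancels | 75.0% | 0 |

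The bias comes from unequal multiplicity, not from multiplicity as such.

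**Step 3. Check the interval.** The naive half-width treats every lesion as independent: 1.645 × √(s(1 − s)/L), where s is the lesion-level sensitivity and L = 51 × (0.75 m1 + 0.25 m0). The comparator is a ratio-estimator half-width that respects the person as cluster: 1.645 × √(E/51)/(0.75 m1 + 0.25 m0), with E = 0.75 (m1² + v1)(1 − s)² + 0.25 (m0² + v0) s². The between-person variance of lesion numbers is either zero (v1 = v0 = 0) or Poisson for the extra lesions (v1 = m1 − 1, v0 = m0 − 1).

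| m1 | m0 | Naive | Clustered |
|---|---|---|---|
| 1.25 | 1 | ±8.6 | ±8.8 to ±9.0 |
| 1.5 | 1 | ±7.6 | ±7.9 to ±8.1 |
| 2.0 | 1 | ±6.1 | ±6.5 to ±6.7 |
| 1.25 | 1.25 | ±8.9 | ±10.0 to ±10.7 |
| 1.5 | 1.5 | ±8.1 | ±10.0 to ±11.0 |

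With extra lesions in positives only, the naive interval is about 0.2 to 0.6 points too narrow. With equal multiplicity the understatement is larger (about 1.9 to 2.9 points at 1.5), but the estimate is then unbiased.

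**Step 4. If the target of 51 were filled with lesions.** At 1.25 lesions per affected person in both groups, 51/1.25 = 40.8 people stand behind the count. The person-level half-width would be 1.645 × √(0.1875/40.8) = ±11.2 points, which misses the ±10 requirement.

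**The case against.** The strongest reply is that the authors meant people. The sample size section uses the same nouns for its 51 cases and then adds them to non-cases to obtain patients. On that reading, item 3 uses the number of cancers loosely for the number of people with cancer, and no lesion-level analysis is planned. This is plausible, and it makes the point one of wording rather than a flaw in the design. It does not remove the point: the stated definition of a main outcome still counts lesions, its neighbours count participants, and no counting rule settles the matter.

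A reader might go further and infer that sensitivity will be inflated because extra lesions can only enter the detected side. The definition does not say that. It counts all lesions after a negative screen, so several in one screen-negative person would all enter the denominator. The upward bias needs unequal multiplicity. Unequal work-up makes that plausible, but the protocol does not establish it.

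A reader might also infer that the interval shrinks falsely from ±10 to ±7.6 or ±6.1 points. The protocol names no interval method for the analysis and never says that lesions will be treated as independent. Most of that drop is also not false precision: the quantity being estimated has moved away from 75%, and its correct interval is narrower too (±7.9 to ±8.1 and ±6.5 to ±6.7).

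Finally, the low end of the assumed range matters. At 1.1 or 1.25 lesions per affected screen-positive, the shift of 1.7 or 3.9 points lies well inside the planned ±10.

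**Conclusion.** The point stands as an inconsistency of unit with a possible upward bias. As written, item 3 does not give the person-level sensitivity for which the study was sized, and it does not share a 2x2 table with specificity.

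The bias is conditional. It requires that the wording be followed literally and that affected screen-positives have more recorded lesions each than affected screen-negatives. It is 1.7 to 10.7 points for 1.1 to 2.0 lesions per affected screen-positive against one per affected screen-negative, and zero if multiplicity is equal. These multiplicities are assumptions, and the documents give no basis for choosing among them.

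Understated uncertainty is a secondary matter. It arises only if lesions are analysed as independent, and it is small when multiplicity is confined to positives. The figure of 51 and the group totals are arithmetically sound and are not in question.

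**What to change.** Reword item 3 per participant: sensitivity is the number of participants with a positive screen and at least one colorectal cancer or advanced neoplasm, divided by all participants with at least one such lesion within the follow-up window. Classify each participant by the most advanced lesion, and report lesion counts descriptively only.

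The cost is one sentence. The sample size does not change, because the 51 cases per group and their half-width of about ±10 points already refer to people.

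The change does not cure the separate problem that positives and negatives are verified differently (colonoscopy against clinical follow-up and registry linkage). That can raise sensitivity even when people are counted, and it needs its own treatment.

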##### Diagnostic procedures

All participants with positive iFOBT screens will be invited to undergo subsequent diagnostic colonoscopies. If polyps are found, polypectomies will be conducted at the time of the diagnostic procedure. If advanced mucosal neoplasia is found, it will be planned for endoscopic mucosal resection (EMR) at a separate procedure. Advanced neoplasia is defined as adenoma with at least one of the following features: 1 cm or more in size, tubulovillous or villous components, or high-grade dysplasia, or any advanced neoplasm 1 cm or more in diameter. EMR is used increasingly frequently for minimally invasive curative resection of benign and early-stage malignant lesions (T1a) throughout the gastrointestinal tract. EMR has the advantage of managing large, sessile polyps in the outpatient setting, which is potentially cost-saving and may improve clinical outcomes in this high risk cohort(36).

All cancers identified will be staged and the participants will be referred to the colorectal surgical and oncology team, depending upon the stage of initial diagnoses. All cancer diagnoses will be reported to the Central Cancer Registry of New South Wales (located within the Cancer Institute of NSW) for all patients with CKD, and the Australia and New Zealand Dialysis and Transplant Registry (ANZDATA) for those on renal replacement therapy (CKD-dialysis and CKD-transplant). The ANZDATA registry is comprehensive database that prospectively collects information on all patients on renal replacement therapy in Australia and New Zealand since 1963. The clinical data includes records of all new cancers except for squamous and basal cell carcinomas. Notification of malignant cancers is a statutory requirement for all health-related institutions in New South Wales. The Central Cancer Registry of New South Wales contains all cancer records and the identifying information for patients diagnosed and treated with cancer within the state of New South Wales since 1972.

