##### Reference standard

Clinical follow-up will be the reference standard for all participants. All participants, with or without screen positive results, will be followed clinically two years after their initial screen. To ensure adequate follow-up and accurate calculation of the screening test performance characteristics of cancer, we will compare our records with that of the Central Cancer Registry (CCR) of NSW through data linkage at 2, 5 and 7 years after the initial screens with the attempt to capture all cancer diagnoses.

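### The sensitivity formula omits screen-positive participants whose disease is first confirmed in follow-up, although the plan's own reference standard makes them true positives

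*Protocol article*

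**What the plan says.** All references are to Study design 1 of the Protocol article.

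- **Reference standard.** "Clinical follow-up will be the reference standard for all participants". The section continues: "All participants, with or without screen positive results, will be followed clinically two years after their initial screen". Cancer registry records are added "through data linkage at 2, 5 and 7 years after the initial screens with the attempt to capture all cancer diagnoses".
- **Diagnostic procedures.** "All participants with positive iFOBT screens will be invited to undergo subsequent diagnostic colonoscopies". No uptake or completion rate is stated, and no colonoscopy is described for screen-negatives.
- **Outcomes, item 3 (sensitivity).** The numerator is "the number of colorectal cancers and/or advanced neoplasms detected through screening". The denominator is that same number plus "the total number of cancers and/or advanced neoplasms occurring within the delay in a given period (the follow-up time) after a negative screen".
- **Outcomes, item 4 (specificity).** Every term is restricted to people free of disease over follow-up. For screen-positives the term is "the number of participants without colorectal cancers and/or advanced neoplasms after a positive screen within the follow-up period".
- **Statistical analyses and sample size calculations.** For each of the three patient groups, "the sensitivity is expected to be 75% and the maximum required 90% confidence interval width is ± 10" per cent, which is said to need 51 diseased cases.

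**The concern.** The first aim is to measure how well the iFOBT separates diseased from disease-free people with CKD. That requires crossing the iFOBT result with disease status under the reference standard. Item 4 does so for screen-positives: follow-up decides that they are disease-free. Item 3 does not: follow-up is never used to decide that a screen-positive is diseased.

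The people affected had a positive iFOBT and then declined colonoscopy, never completed it, or had a lesion missed, and were later diagnosed clinically or through the registry. Such cases are foreseeable. Colonoscopy is by invitation, and the article's own background section warns that it may be harmful after a positive iFOBT in people with reduced kidney function and cardiac disease. The exclusion of people medically unfit for colonoscopy reduces the number but does not rule such cases out.

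If item 3 is applied as written, a failure of the diagnostic work-up is charged to the stool test. The sensitivity also feeds the economic model in Study design 2, which simulates the diagnostic process. If colonoscopy non-uptake or misses are modelled there too, they would be counted twice.

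**Working it through.** **1. Where the case falls.** Take an iFOBT-positive participant whose disease is first confirmed in follow-up, and test that person against each term.

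| Term | Requirement | Met? |
|---|---|---|
| Item 3, numerator and first part of denominator | Lesion found by screening | No: found clinically or by registry |
| Item 3, second part of denominator | Lesion in follow-up, screen negative | No: screen was positive |
| Item 4, screen-negative term | Disease-free, screen negative | No |
| Item 4, screen-positive term | Disease-free, screen positive | No: diseased |

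Absence from item 4 is correct, because a diseased person does not belong in specificity. Absence from item 3 is the fault.

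**2. The plan's own figure.** Inputs from the sample size section: sensitivity p = 0.75, half-width d = 0.10, 90% confidence (z = 1.645).

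n = z² p(1 − p)/d² = 1.645² × 0.75 × 0.25 / 0.10² = 50.7, rounded up to 51. The stated 51 reproduces.

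Expected true positives TP = 0.75 × 51 = 38.25. Expected false negatives FN = 51 − 38.25 = 12.75.

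**3. Effect of one omitted case.** Removing one true positive from both numerator and denominator lowers the ratio by

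TP/n − (TP − 1)/(n − 1) = FN/[n(n − 1)] = 12.75/(51 × 50) = 0.005, or 0.5 points.

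This is positive whenever FN > 0, so the direction of this omission, taken alone, is always downward. In whole numbers, 38/51 = 74.5% becomes 37/50 = 74.0% with one case omitted and 34/47 = 72.3% with four.

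**4. Effect of an assumed share.** Let f be the share of true positives confirmed only in follow-up. The documents give no value for f. The 68% participation rate in the sample size section concerns taking part in screening, not colonoscopy uptake, so it cannot stand in for f.

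Sensitivity as written = 38.25(1 − f) / [38.25(1 − f) + 12.75]. Half-width = 1.645 × √[s(1 − s)/cases left], where s is that sensitivity.

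| f (assumed) | Cases omitted | Cases left | Sensitivity as written | 90% half-width |
|---|---|---|---|---|
| 0% | 0 | 51 | 75.0% | ±10.0 |
| 5% | 1.9 | 49.1 | 74.0% | ±10.3 |
| 10% | 3.8 | 47.2 | 73.0% | ±10.6 |
| 20% | 7.7 | 43.4 | 70.6% | ±11.4 |

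Because 51 is the bare minimum for ±10 points, each omitted case also costs precision.

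**The case against.** **The wording is open.** The article does not define what counts as found by screening. If it meant any disease in a participant with a positive iFOBT, the gap would close, and the Reference standard section, which applies follow-up to everyone, gives an analyst some ground for reading it so. This stands as a possible reading, but the text does not state it. An analysis plan that is not shown may settle case classification. The formula the article does state conflicts, on its ordinary meaning, with the article's own standard.

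**The affected set is narrow.** A lesion found at a delayed or repeated colonoscopy within the work-up is still screen-detected. This stands, and such cases are not part of the point.

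**The size is assumed and mostly concerns cancer.** This stands. The registry holds cancer records, and follow-up will rarely bring a missed advanced adenoma to light. The table applies f to the whole composite of 51 cases, so its larger shares may be too high for that endpoint. The documents do not split the 51 into cancers and advanced neoplasms. Even at f = 20% the shift of 4.4 points is less than half the planned half-width of 10.

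**Late cancers may be new disease.** This stands too. After a clear colonoscopy, a cancer first seen at the 5- or 7-year linkage need not have been present at the screen. The true-positive label is firmest within two years. The same doubt applies to late cancers in screen-negatives, which item 3 counts as false negatives over a follow-up period it does not fix.

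**A stronger reading to avoid.** A reader might infer that the study's sensitivity is biased downward overall. The documents do not support that. Screen-negatives have clinical follow-up and linkage but no planned colonoscopy, so silent advanced neoplasms among them go uncounted, which pushes sensitivity up. The net bias may be upward. A reader might also infer that item 4 is at fault because it too leaves these people out; it is not.

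**Conclusion.** The point holds in a limited form. On its ordinary reading, item 3 conflicts with the reference standard and drops participants who are test-positive and diseased under that standard. Taken alone, the cost is about 0.5 points of sensitivity per omitted case in a 51-case group: 1.0, 2.0 or 4.4 points if 5%, 10% or 20% of true positives are affected, with the half-width widening from ±10.0 to as much as ±11.4. These figures rest on the plan's 75% and 51 cases and on assumed shares that the documents can neither confirm nor bound. The effect is small if few cases arise, and it falls mainly on sensitivity for cancer. It should be corrected because it concerns a main accuracy measure under the first aim and is avoidable, not because it is shown to determine the study's overall bias.

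**What to change.** Reword Outcomes item 3 so that sensitivity is defined by iFOBT result against disease status under the reference standard, within one fixed window applied equally to screen-positives and screen-negatives.

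- **Numerator:** iFOBT-positive participants with cancer or advanced neoplasia confirmed at colonoscopy, or by clinical follow-up or registry linkage within the window.
- **Denominator:** that number plus iFOBT-negative participants with disease confirmed in the same window.
- **Window:** for example, the two-year clinical follow-up for the main estimate, with the 5- and 7-year linkages as secondary estimates.
- **Separate figure:** report the yield of the screening colonoscopy as a detection measure, so that failures of work-up remain visible without being charged to the iFOBT.

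Item 4 needs no change on this account beyond using the same window. The cost is a rewording: follow-up and linkage are already planned for screen-positives, so no new data are needed.
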